#### Economic analysis

An early economic analysis [44] will aim to identify the indicative estimates of the incremental costs and consequences and key drivers of the cost-effectiveness of a risk-stratified NHSBSP compared with the usual NHSBSP. A decision-analytic model-based cost-effectiveness analysis will capture the incremental NHS costs and consequences for a cohort of women eligible for NHSBSP in the UK over a life-time horizon. A decision-analytic model (a decision-tree combined with a published model) [11] will be structured to represent the care pathways of current NHSBSP practice (no risk feedback) and the proposed BC-Predict intervention in a sample of women eligible for the NHSBSP. The cost of the risk-stratified NHSBSP will be identified using a micro-costing study [45] and take account of the cost of the addition of SNPs to the risk estimation algorithm. The decision-tree will recognise the uptake of appropriate healthcare services (General Practice contact; FHRP Clinic referral and proportion of women starting chemopreventive medication e.g. anastrozole/tamoxifen/raloxifene). A published model [9] will be used to understand the lifetime impact on NHS costs and patient consequences of using different screening intervals based on risk-prediction, or usual NHSBSP. Using an economic model allows data assimilation from various sources (BC-Predict and systematic reviews; structured expert elicitation methods [46]) in a structured framework [47]. The model-base case analysis will focus on changes in health status (using EQ-5D-5 L) but explore the impact on capability (ICECAP-A) in a scenario analysis. These data will be obtained from the self-reported outcomes (health status (EQ-5D5L) [34]; capability (ICECAP-A) [35]) collected in the prospective study (see Table 1) and supplemented with published data to allow estimation of the impact on a life-time horizon. The EQ-5D5L [34] and ICECAP-A [35] have published preference weights that will allow calculation of quality adjusted life years for health and capability with and without the intervention. Parameter uncertainty in the decision-tree component of the model will be quantified using probabilistic sensitivity analysis for the base case analysis and scenario (capability) analysis. These two outcomes (health and capability) will then be used in two distinct value of information analyses (Expected Value of Perfect Information (EVPI) and expected value of partial perfect information (EVPPI)). The EVPI represents the maximum amount that should be spent on future research to gain perfect information to eliminate the possibility of a wrong (funding) decision. Further steps are then necessary to understand key parameters driving the uncertainty. This involves estimating the EVPPI that tells a decision maker which parameters are contributing to the uncertainty in the model and help to guide what type of additional evidence is most valuable.

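### Probabilistic analysis is stated only for the decision tree, so the planned EVPI is a partial value conditional on the lifetime model, not a ceiling on research spending

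*Protocol article*

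**What the plan says.** The point rests on the Economic analysis section, under Analysis plan and power calculations, read in order.

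- **Structure.** "A decision-analytic model (a decision-tree combined with a published model) [11] will be structured to represent the care pathways". The aim is to capture "incremental NHS costs and consequences for a cohort of women eligible for NHSBSP in the UK over a life-time horizon".
- **Tree.** "The decision-tree will recognise the uptake of appropriate healthcare services", with GP contact, clinic referral and starting chemoprevention given as the services.
- **Lifetime part.** "A published model [9] will be used to understand the lifetime impact on NHS costs and patient consequences of using different screening intervals".
- **Scope of the probabilistic analysis.** "Parameter uncertainty in the decision-tree component of the model will be quantified using probabilistic sensitivity analysis", both for the base case and for the capability scenario.
- **Next step.** "These two outcomes (health and capability) will then be used in two distinct value of information analyses", namely EVPI and EVPPI.
- **Interpretation.** "The EVPI represents the maximum amount that should be spent on future research". EVPPI is said to tell the decision maker which parameters contribute to uncertainty in the model, without limiting this to the tree.

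The study objectives on NHS costs and patient consequences list the key drivers of cost-effectiveness, the extent of uncertainty in the evidence and the potential value of future research.

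**The concern.** EVPI is defined over all the parameters that are uncertain in the decision. Here the probabilistic analysis is expressly limited to one of two components, and the other component generates the lifetime costs and consequences. A value computed that way answers a narrower question: what it would be worth to resolve the tree parameters, given the lifetime model. The section then gives the result the meaning that belongs to the wider quantity.

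Three stated objectives depend on this. A parameter that is not varied cannot appear as a driver. Uncertainty that is not propagated is absent from the stated extent of uncertainty. The value of future research would omit whatever could be learned about the lifetime component. The Background says a definitive study would look at effects on breast cancer incidence and stage. If those consequences sit mainly in the published model, which is the natural reading but is not spelled out, the planned analysis would give little weight to the uncertainty that study is meant to resolve.

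**Working it through.** **No figure to reproduce.** The article gives no net benefit, threshold, parameter distribution or EVPI. The check is therefore of the definition, followed by illustrations on assumed inputs.

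**1. Definition.** With net benefit NB(d, θ) for option d:

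EVPI = E[max over d of NB(d, θ)] − max over d of E[NB(d, θ)].

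Split θ into tree and lifetime parameters. Perfect information on the tree alone is worth

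E_tree[max over d of E(NB | tree)] − max over d of E[NB(d, θ)].

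By Jensen's inequality the first term is no larger than the first term of EVPI, so a proper partial value never exceeds the full EVPI. The two agree only if the lifetime parameters add no decision uncertainty. The article does not claim that.

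**2. Additive normal illustration (all inputs assumed).** Let incremental net benefit be normal with mean m and SD s = 100 per woman, the sum of independent tree and lifetime parts. The tree carries a share f of the variance, so s_tree = 100√f. Then

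EVPI(m, s) = s·φ(m/s) − |m|·Φ(−|m|/s).

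Worked case, m = 50 and f = 0.25, so s_tree = 50:
- tree only: 50 × 0.2420 − 50 × 0.1587 = 4.17
- full: 100 × 0.3521 − 50 × 0.3085 = 19.78
- ratio: 4.17 / 19.78 = 21%

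| Mean m | Full EVPI | f = 10% | f = 25% | f = 50% | f = 75% |
|---|---|---|---|---|---|
| 0 | 39.89 | 12.62 (32%) | 19.95 (50%) | 28.21 (71%) | 34.55 (87%) |
| 50 | 19.78 | 0.77 (4%) | 4.17 (21%) | 9.98 (50%) | 15.15 (77%) |
| 100 | 8.33 | 0.01 (0.1%) | 0.42 (5%) | 2.51 (30%) | 5.33 (64%) |

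At f = 100% the two values coincide.

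**3. Multiplicative illustration (all inputs assumed).** Incremental net benefit = uptake × QALY gain × 20,000 − cost. Uptake is Beta(40, 60), QALY gain is Normal(0.006, 0.006), cost is Gamma with shape 25 and scale 2, and there are 2,000,000 draws. Mean: 0.4 × 0.006 × 20,000 − 50 = −2. Varying everything gives an EVPI of 18.76 per woman. Holding the QALY gain at 0.006 gives 3.65, which is 3.65 / 18.76 = 19%.

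**4. Direction is not guaranteed.** If the lifetime model is non-linear and is run at point estimates, the mean net benefit itself can shift. Using the table: suppose the true mean is 100 (full EVPI 8.33), but point estimates move it to 0 with f = 25%. The reported value would be 19.95, above the full EVPI. The shift is an assumption, chosen to show that an error upward is possible.

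**The case against.** The best reply has five parts.

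- **The article does not say that the lifetime inputs are fixed.** This is correct. Uncertainty could enter as distributions on lifetime cost and QALY payoffs at the end of the tree, and a fuller health-economics plan might say so. But the article itself fixes the scope by naming the decision-tree component, and nothing in it extends that scope. The conclusion must be conditional; it does not fall away.
- **The sentence on maximum spending is a general definition, and a correct one.** This also stands, so there is no reason to delete it. The difficulty is that it is the only reading offered for the planned result.
- **The varied inputs may go beyond service uptake.** A reader might infer that only uptake, referral and starting chemoprevention are varied. The section lists these as services the tree recognises, not as the full set of parameters. Micro-costing, EQ-5D-5L, ICECAP-A and expert elicitation are also described, without saying which component they enter.
- **Sensitivity analysis is planned elsewhere.** The extensive sensitivity analysis belongs to sub-study three, on the screening interval for low-risk women. It is not called probabilistic and is not tied to EVPI.
- **This is an early analysis giving indicative estimates within a feasibility study.** True, and it lowers the stakes. Even so, the value of future research is one of the study's stated objectives.

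**Conclusion.** The concern holds in conditional form. Unless uncertainty in the published lifetime model is propagated, the planned EVPI is a value of information for decision-tree parameters conditional on that model. It is not a valid maximum for research spending, and the matching EVPPI cannot identify lifetime-model parameters as drivers. This conflicts with the interpretation given in the same section.

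Two stronger readings are tempting and are not supported. One is that the plan will certainly understate the value of research. Understatement is certain only for a proper partial value, or when lifetime inputs enter linearly and independently; with a non-linear model run at point estimates the error could go either way. The other is that the shortfall has a known size. It does not: the percentages in the working rest wholly on assumed variance shares, means and distributions. They show that the gap can be anything from negligible to almost total, and say nothing about where this model lies.

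**What to change.** Where the published model allows, propagate its uncertainty into the probabilistic analysis, for example as distributions on lifetime cost and QALY payoffs, and compute EVPI and EVPPI jointly over both components. The cost is some extra model runs. The article does not show whether the published model can be run probabilistically, so this has to be established first.

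If it cannot, keep the general definition of EVPI, but state that the reported value is partial and conditional on the lifetime model. Limit the EVPPI claim to decision-tree parameters, and do not present the figure as the maximum worth spending on research. This costs wording only.

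If lifetime uncertainty is already meant to enter, a sentence saying how would settle the point.

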
### Three sub-studies

The present research also includes sub-studies. Although integral to the overall research, they are described here, to facilitate clear presentation of their aims and methods.

### Sub-study one: incorporation of SNP information into BC-predict risk estimates

#### Objectives

To determine uptake and acceptability of a DNA based risk estimate as part of routine NHSBSP appointments, and to quantify the higher proportions of women at high/moderate and lower risk obtained by adding SNP information.

#### Background

A subset of women will have the option to provide a sample of saliva from which DNA can be extracted. DNA will be extracted with standard techniques and currently known breast cancer SNPs associated with breast cancer typed. The results of this testing will be incorporated into the BC-Predict risk algorithm. Adding a genetic SNP score from a saliva sample to other risk factors not only potentially increases the accuracy of risk estimation, but also increases the discrimination of risk estimation, so that more women are identified as being at higher or lower risk, and fewer identified as being at population-average risk. It thereby increases the proportion of women identified at high-risk who can benefit from being offered NICE approved additional screening and drug prevention from 4 to 6%.

#### Methods

In total, it is expected that 1000 women will provide a DNA sample and receive a personalised breast cancer risk estimate incorporating their Polygenic Risk Score. All women invited for screening at Withington Community Hospital and Oldham Integrated Care Centre will be potentially eligible for the SNP sub-study, however, this will only be offered to women on a pragmatic basis depending on whether a member of staff is on site to assist with taking consent. A separate paper consent form will be completed by the participant in addition to the online consent form for the main study. Women giving their consent will be provided with an Oragene kit to place their salivary sample. They will be guided on site by a member of staff as to how to complete the sample.

#### Methods: data analysis

The proportion of women in the 1000 providing saliva DNA who are classified as NICE actionable high and moderate risk as well as below average risk will be compared to their classification without a SNP Polygenic Risk Score. Chi square statistics will compare the difference between risk categories with and without the addition of the SNP Polygenic Risk Score. These data will also be used in the proposed economic analysis.

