Arguably, the most difficult to collect core outcome is 9, the proportion taking up chemoprevention. On the basis of PROCAS results we would anticipate that 1169 of the 8000 who consent to BC-Predict would have sufficient risk to be considered for chemoprevention and that 10% of these would take it up [8, 38, 39]. Thus 117 of the 8000 women (1.5%) receiving the intervention might be expected to be prescribed chemoprevention. It is anticipated that very few in the 18,700 sent the standard screening invitation would be prescribed chemoprevention, but even if as many as 0.9% did so, we would have 90% power to detect this as significant at 5% level with two-sided testing, and 80% power if 10% took up chemoprevention. The Greater Manchester Medicines Management group has agreed a shared care protocol stating that the initial prescription of tamoxifen and anastrozole should be made by a FHRP specialist. As such data from even those in the control arm should be available from prescriptions made in the FHRP clinics.

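### SNP sub-study: each woman is classified twice, but the plan names only chi-square statistics and no paired test

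*Protocol article*

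**What the plan says.** The objective of sub-study one is partly "to quantify the higher proportions of women at high/moderate and lower risk obtained by adding SNP information". Its Background section expects the proportion of women who can be "offered NICE approved additional screening and drug prevention from 4 to 6" per cent to rise by that amount. Its Methods section gives the size: "In total, it is expected that 1000 women will provide a DNA sample".

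The data-analysis section takes these women's high, moderate and below-average classifications with the SNP score, which "will be compared to their classification without a SNP Polygenic Risk Score". The test follows in one sentence: "Chi square statistics will compare the difference between risk categories with and without the addition of the SNP Polygenic Risk Score". The article then says that the data will also go into the economic analysis.

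For this sub-study the article gives no significance level, power, or expected number of women changing category.

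**The concern.** Each woman is her own comparator, so the two classifications are correlated. They share the questionnaire answers and, where available, breast density; only the SNP score differs.

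Without a qualifier, a chi-square statistic is normally taken to be Pearson's. Applied to the two distributions side by side, it counts 1,000 women as 2,000 independent ones. It still addresses whether the proportions differ, but with the variance for independent groups. When the classifications are positively correlated, that variance is too large. A real shift may then be missed, and any interval built on the same variance is wider than the data warrant. In a sub-study meant to show what SNPs add, that loses information already collected.

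**Working it through.** The plan gives no power figure for this sub-study, so there is none to reproduce.

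**Inputs from the article.** n = 1,000 women. High risk is 4% without and 6% with SNPs, so d = 0.02.

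**Assumptions.**
- Two-sided 5% level. The article states this ("significant at 5% level with two-sided testing") only for core outcome 9.
- The proportion high risk by both methods, p11, is not given and is varied. The discordance is ψ = (0.04 − p11) + (0.06 − p11). The article says only that SNPs spread women out, "so that more women are identified as being at higher or lower risk, and fewer identified as being at population-average risk".

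**Step 1. Unpaired test.** The pooled standard error is √(2 × 0.05 × 0.95 / 1,000) = 0.00975. Significance therefore needs a difference above 1.96 × 0.00975 = 0.0191. If the samples really were independent, the standard error of the difference would be √[(0.04 × 0.96 + 0.06 × 0.94) / 1,000] = 0.00974. Power would be Φ[(0.02 − 0.0191) / 0.00974] = 53.7%. Reaching 80% would take 1,863 per group.

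**Step 2. Paired test.** The true standard error of the difference is √[(ψ − d²)/n]. McNemar power is approximately Φ[(d√n − 1.96√ψ) / √(ψ − d²)]. For p11 = 3%, ψ = 0.04 and power = Φ[(0.632 − 0.392) / 0.199] = 89% (90% simulated). For p11 = 1.5%, ψ = 0.07 and power = Φ[(0.632 − 0.519) / 0.264] = 67%.

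**Step 3. Both tests on the same simulated paired data, 4% v 6%.**

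| High by both | Discordance ψ | Unpaired chi-square power | McNemar power |
|---|---|---|---|
| 3.0% | 4% | 56% | 90% |
| 2.5% | 5% | 56% | 82% |
| 2.0% | 6% | 55% | 74% |
| 1.5% | 7% | 54% | 67% |
| 0.24% (zero correlation) | 9.5% | 54% | 54% |

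The last row uses p11 = 0.04 × 0.06 = 0.0024. There the two tests coincide.

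**Step 4. Rejection rate under no change, 5% v 5%.** The unpaired test still requires a difference above 0.0191, but the true standard error is √(ψ/n).
- With 3.5% high by both, ψ = 0.03, the threshold lies at 0.0191 / 0.00548 = 3.49 standard errors, and the test rejects about 0.05% of the time.
- With 2% high by both, ψ = 0.06, the threshold lies at 0.0191 / 0.00775 = 2.47 standard errors, and it rejects about 1.4% of the time.

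McNemar's test stays at about 5% in both cases.

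**Step 5. One data set.** Suppose 40 women are high risk without SNPs and 60 with.
- Pearson gives X² = 4.21, p = 0.040, whatever the cross-table.
- McNemar with 10 moving down and 30 up gives (30 − 10)²/40 = 10.0, p = 0.0016.
- McNemar with 20 down and 40 up gives (40 − 20)²/60 = 6.67, p = 0.0098.
- The estimated shift is 2 points in every case. Its 95% CI is 0.09 to 3.91 points if pairing is ignored, and 0.77 to 3.23 if it is used with 10 down and 30 up.

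**The case against.** The strongest reply is that the article never says the test is for independent groups. McNemar, Stuart-Maxwell and Bowker statistics are all referred to a chi-square distribution, and the sentence before the test shows that the authors know the comparison is within women. The wording is thus compatible with a paired test, and a condensed article may leave the exact variant to the full protocol. This stands in part: the text is ambiguous, not explicitly wrong. But the article did choose to name a test, the ordinary meaning of that name does not fit the design, and a reader cannot tell that a paired version is meant.

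A reader might infer that the plan risks false claims about SNPs. It does not: under positive correlation the unpaired test rejects too rarely. A reader might also infer that the economic model would be contaminated. The article says that the data will be used there, and nothing in it passes a test statistic or its standard error into the model. The proportions are the same under any test.

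It is also fair that the 4% to 6% shift is a background expectation, not a design hypothesis, and that the power loss depends on a discordance the article does not give. At 8% discordance McNemar reaches only 61%. Near-zero correlation is implausible for two scores sharing all their other inputs, but an unconditional claim of large power loss is not supported.

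**Conclusion.** The point holds as a mismatch between a paired design and an unqualified test name. If the test is Pearson's, it is conservative. At the article's own shift it has about 55% power, where a paired test on the same women has about 67% to 90%, provided that 1.5% to 3% are high risk by both methods. Outside that assumed range the gap widens as the two classifications agree more, and closes as their correlation falls to zero. If a paired test was intended, only the wording is at fault.

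Severity is minor to moderate. No core outcome depends on this analysis, no power is claimed for it, no stated figure is wrong, and the objective is mainly to estimate proportions, which are not biased.

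**What to change.** In the data-analysis section of sub-study one, state that the comparison is paired within woman, and replace the chi-square sentence with:

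- McNemar's test and the paired difference in proportions with its 95% CI at each cut: high (≥8%), moderate or high (≥5%), and below average (<2%);
- the Stuart-Maxwell test of marginal homogeneity for the shift across the four risk categories;
- the full cross-table of categories without and with the SNP score, so that movement in both directions is visible.

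The cost is wording only. The same women and the same data are used.

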### Sub-study two: understanding acceptability and implementation of BC-predict

#### Objectives

The main objectives are to explore service users’ views on acceptability of BC-Predict (interviews) and to assess the perceived impact of BC-Predict on the NHSBSP, FHRP Clinics and General Practice (focus groups).

#### Background

In addition to the quantitative measures of impact of BC-Predict, we will also carry out qualitative work as part of a process evaluation to understand the key issues behind successful implementation of the BC-Predict system [48]. The qualitative work will comprise one-to-one interviews with NHSBSP service users to explore acceptability of BC-Predict amongst women at varying levels of risk, where there is currently a dearth of evidence [49]. It will also employ focus groups with healthcare professionals to investigate the implementation, delivery and impact of BC-Predict on the current NHSBSP. This qualitative work will give insight into capacity issues, indication of the training and support required to deliver BC-Predict on a larger scale, as well as communication challenges and pathways for both service users and healthcare professionals. This will enable us to build an evidence base to inform practice and policy should BC-Predict be rolled out to the wider NHSBSP.

#### Methods

##### Patient interviews: design, sample, recruitment and data collection

A purposive sample of below average, average, moderate and high-risk women who had received BC-Predict will be invited to participate in a semi-structured interview. Below average and average risk women will be invited for interview 1 month after receiving their risk feedback letter. Moderate-risk and high-risk women will be invited for interview 6 months after receiving their risk feedback letter. This gives women in the moderate and high-risk groups the chance to explore extra screening options or medications prior to the interview. The BC-Predict online platform allows easy identification of women in each risk group in each location. We will aim to recruit up to 40 women to these interviews (up to 10 women per group) with variation in which study sites to which women were invited. In addition, questionnaire responses will guide sampling to allow variation in uptake of chemoprevention.

Data will be collected by semi-structured interview either face-to-face or over the phone, audio recorded and transcribed verbatim. The decision to stop recruitment will be based on whether the data collected is sufficient to answer the research questions and aims [50]. Therefore the depth of the data will be used as an indicator to cease recruitment. The decision to end recruitment will also be based on the active exploration of negative cases, as well as when there appears to be no new content being discussed in the final interviews of each risk group. All interviews will cover core issues including acceptability of BC-Predict and lifestyle modifications. Other issues will be covered are those that are most relevant to the risk estimate communicated, e.g. uptake of chemoprevention (e.g. GP advice) in higher risk women, and reassurance in below-average risk women. We will be sensitive to considering naturally occurring variation, e.g. women recruited differently due to SNP collection or across different study sites, or from diverse ethnic backgrounds.

